2. to compare pain, disability, quality of life, grip strength, number of complications and cast changes after DRF treated with these two different cast positions
3. to assess the effect of PCS on the functional outcome of conservatively treated DRFs and the possible interaction between PCS and the functional outcome of DRF treatment with two different cast positions
4. **PRIMARY HYPOTHESES**

Our primary null hypotheses are as follows:

1. functional cast position gives similar functional outcome than currently used flexion-ulnar deviation cast position
2. functional cast position yields to similar results to currently used flexion-ulnar deviation cast position with regard to quality of life and grip strength and also with lower rates of complications and number of cast changes during immobilization when treating DRFs.
3. high PCS does not have an interaction with functional outcome on the patient rated wrist evaluation (PRWE) scale after adjusting for cast position used in the conservative treatment
4. **STUDY DESIGN**

The study is a pragmatic, prospective, randomized, controlled, multi-center trial. It is aimed to compare two different positions of a cast. The two cast positions compared are flexion-ulnar deviation position (widely used in Finland) and functional position used in other Nordic countries.

Primary outcome in this study is PRWE score measured after one and two years. Secondary outcomes measured are disability [Quick-DASH (disabilities of the arm, shoulder and arm)], pain in visual analogue scale (VAS), PCS, quality of life (15-D), complications and number of surgical interventions and cast changes. Subgroup analysis will be performed to find out patient specific features indicating good or worse outcome. PCS is used to assess the presence of possible mental susceptibility possibly influencing to the functional outcome.

1. **RESEARCH METHODS AND MATERIAL**
   1. **PATIENT SELECTION**

The eligible study population will consist of all consecutively (aged 65 or more) treated patients with a DRF identified in the public or referral emergency departments of participating hospitals.

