In this trial, a validated wrist specific PRWE-score is used as the primary outcome measure. Just recently Wallenkamp and coworkers published a report, where minimal clinically important difference in PRWE was set at 11 points with SD of 14 [37]. Based on power calculations (Cl 95%, power 0.95, SD 14) required sample size per group is 40 patients. Assuming 30% of drop-out due to possible surgical interventions during cast treatment, group size would be 52 per group (total 104). In case of patient cross-over, patients will be analyzed according to the intention-to-treat principle.

- 1. **ANALYSIS OF THE MATERIAL**

Each patient will get an initial trial identification number (TIN) which is matched with actual patient identification (ID). **The matching key is stored in study nurse’s office in Tampere University Hospital. Patients are handled only with TIN during follow-up period and analyzing the of the material. Results are given only in general level with mean values thus individual patient’s information is not able to be extracted. The electronical registry contains x-rays and it is located in hospital’s secure server. The research data will be deleted 15 years after the end of the study.**

- 1. **STATISTICAL ANALYSIS**

Continuous skewed variables between the groups were compared by the Mann-Whitney *U* test and t-test is used when variables are unskewed. Results are presented with 95% confidence intervals. Two-way-tables with the chi-square test will be used for dichotomous variables. In subgroup analysis the effect of age, sex, fracture group, smoking, and other diseases will be evaluated against the scores and overall quality of life after fracture.

Analysis of covariance will be used to assess the effect of pain catastrophizing score on the outcome of cast treatment. PRWE will be used as a dependent variable, cast as independent and pain catastrophizing score as covariate.

The effect of cast position and PRWE is investigated also in the multivariate manner. Multivariable analysis is performed with linear regression analysis since the outcome variable PRWE is normally distributed. Main variable of interest included is the cast and age, sex, fracture group, smoking and other diseases are used as confounding variables.

- 1. **ETHICAL ISSUES**

The ethical approval of this study is applied with this research plan.

1. **IMPLEMENTATION**
   1. **CONTINGENCY PLAN**

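### The second half of objective 3 asks about a cast-by-PCS interaction, but no planned analysis contains a term that tests it

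*Protocol*

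**What the plan says.** Objective 3 (Protocol, OBJECTIVES) has two parts. The first is the effect of PCS on functional outcome. The second is "the possible interaction between PCS and the functional outcome of DRF treatment with two different cast positions".

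Hypothesis 3 (PRIMARY HYPOTHESES) states that "high PCS does not have an interaction with functional outcome on the patient rated wrist evaluation (PRWE) scale after adjusting for cast position".

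STATISTICAL ANALYSIS gives one analysis involving PCS. Its purpose is stated as follows: "Analysis of covariance will be used to assess the effect of pain catastrophizing score on the outcome of cast treatment". Its terms are then named: "PRWE will be used as a dependent variable, cast as independent and pain catastrophizing score as covariate".

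Two other analyses in that section could in principle have carried the interaction. The subgroup analysis is described thus: "In subgroup analysis the effect of age, sex, fracture group, smoking, and other diseases will be evaluated against the scores". The multivariable regression is described thus: "Main variable of interest included is the cast and age, sex, fracture group, smoking and other diseases are used as confounding variables". PCS is in neither list.

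Under INTERVENTION, the first PCS questionnaire is completed after allocation and after the cast has been made. The assessment table under FOLLOW-UP calls this the baseline measurement and repeats PCS at 3 months, 1 year and 2 years. The ANCOVA description does not say which of these values is the covariate.

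**The concern.** Asking whether PCS interacts with cast position means asking whether the difference between casts changes with PCS, or equivalently whether the PCS slope differs between casts. A model with cast as factor and PCS as covariate has no parameter for that. It reports one PCS slope and one cast difference that holds at every PCS value.

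Two things are at stake. If the slopes do differ, the planned model averages them and the difference goes unseen. And because hypothesis 3 uses the word interaction loosely, a significant PCS coefficient from the ANCOVA could be reported as an interaction, which it is not. If the product term is added only after the results are known, it will be post hoc.

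**Working it through.** The Protocol gives no figure for the interaction, so there is none to reproduce. The check compares model terms with the objective and then asks what the missing term could deliver.

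**1. Terms against objective.** Model A is the stated ANCOVA. Model B adds the product.

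- A: PRWE = b0 + b1·cast + b2·PCS + error
- B: PRWE = b0 + b1·cast + b2·PCS + b3·cast·PCS + error

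With cast coded 0/1, the PCS slope under A is b2 in both casts. Under B it is b2 in one cast and b2 + b3 in the other. The second half of objective 3 is the question whether b3 = 0. Model A contains no b3.

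| Planned analysis | Cast | PCS | Cast x PCS |
|---|---|---|---|
| ANCOVA | yes | yes | not named |
| Subgroup analysis | not stated | not listed | not named |
| Multivariable regression | yes | not listed | not named |

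**2. What model A does with a real interaction.** With equal arms and the same spread of PCS in each, the common slope estimates the average of the two slopes. Take slopes of −5.5 and +5.5 PRWE points per SD of PCS. The difference is 11 and the average is (−5.5 + 5.5)/2 = 0. In a simulation of this case (2000 runs, 40 per arm, residual SD 14, no average cast effect), model A rejected for cast in 5.2% of runs and for PCS in 6.1%, about the nominal 5%. The product term in model B rejected in 91%. This is a deliberately extreme case, chosen to show the mechanism.

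**3. What the added term could detect.** Inputs from POWER ANALYSIS are the SD of 14 ("minimal clinically important difference in PRWE was set at 11 points with SD of 14") and 40 patients per group ("Based on power calculations (Cl 95%, power 0.95, SD 14) required sample size per group is 40 patients"), with 52 per group after inflation. Assumptions: 14 serves as the residual SD, PCS is scaled to SD 1, and the test is two-sided at 5%. The Protocol gives neither a PCS SD nor an expected slope difference.

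- SE(b3) = SD × √(2/n per arm)
- 40 per arm: 14 × √(2/40) = 3.13
- 52 per arm: 14 × √(2/52) = 2.75
- Slope difference detectable with 80% power = (1.96 + 0.84) × SE: about 8.8 points per SD of PCS at 40 per arm and 7.7 at 52 per arm

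The detectable difference is proportional to the residual SD. At 40 per arm, an SD of 12 gives 2.80 × 12 × √(2/40) = 7.5, and an SD of 16 gives 10.0.

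Power for b3 (noncentral t, residual SD 14):

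| Slope difference, PRWE points per SD of PCS | 40 per arm | 52 per arm |
|---|---|---|
| 3 | 16% | 19% |
| 5.5 | 41% | 51% |
| 8 | 71% | 82% |
| 11 | 93% | 98% |

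**The case against.** The strongest reply is that the Protocol never writes main effects only. It names a dependent variable, a factor and a covariate, gives no equation and excludes no product term. Checking equal slopes is an ordinary step in ANCOVA and fits that same term, and exact model terms for a secondary aim often sit in a statistical analysis plan. The stated purpose of the ANCOVA is also only the effect of PCS, so the text does not claim that this model tests the interaction.

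Part of this stands: the common-slope form is the standard reading, not a literal statement. But the Protocol does not leave the PCS model open. It lists the model's variables, and neither that list nor any other planned analysis supplies the term its own objective needs. An analysis plan that followed the text would carry the gap forward.

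A reader might also infer that hypothesis 3 cannot be tested. The documents do not support that. The phrase about adjusting for cast position can be read as a cast-adjusted PCS main effect, which the stated ANCOVA does test. Under Expected results and impact, outcome is expected to correlate with PCS whichever cast is used, which fits that reading. What remains for hypothesis 3 is unclear wording.

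Nor does the gap threaten the trial's main conclusion. The PRWE comparison between casts, the sample size and the data collected do not depend on it.

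**Conclusion.** The concern holds for the second half of objective 3. On the standard reading of the stated ANCOVA, no planned analysis tests whether PCS and cast position interact. The first half of objective 3 is testable as planned, the primary comparison is untouched, and hypothesis 3 needs rewording because it admits two readings. Severity is moderate: this is half of a secondary objective, and it can be repaired before analysis.

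The conclusion about the missing term rests on no numerical assumption. The power figures do: they take 14 as the residual SD, 40 or 52 patients per arm, and slopes per SD of PCS. On those values 80% power needs a slope difference of about 8 to 9 PRWE points per SD of PCS. The trial was not sized for this question, so a non-significant interaction would be weak evidence that none exists.

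**What to change.** - Keep the main-effects ANCOVA for the first half of objective 3, the effect of PCS on PRWE.
- Add a second model, PRWE = cast + PCS + cast x PCS, with PCS continuous and centred. Report the interaction coefficient with its 95% CI and label it exploratory.
- Use the first PCS measurement in the interaction model, not the 3-month or later ones. State that it is taken after allocation and casting, so it is not strictly a pre-treatment value.
- Reword hypothesis 3 as two nulls: no association of PCS with PRWE, and no cast x PCS interaction. Reserve the word interaction for the second.

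The cost is one extra model and a rewritten hypothesis, with no new data and no change to the sample size. The change should be made before the outcome data are analysed.

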**Following criteria is used in patient selection:**

Inclusion criteria:

- low energy intra- or extra-articular dorsally displaced DRF within 3cm of the radiocarpal joint, diagnosed with lateral and posterior-anterior radiographs in emergency room (ER)
- physician on call (general practician (GP), acute physician, orthopedic resident or orthopaedic consultant) thinks patient could be appropriate for conservative treatment

Exclusion criteria:

- Operative treatment
- Refuse to participate the study
- Open fracture more than Gustilo 1 gradus
- Age 64 or less
- Chauffeure’s or Barton´s fracture
- Smith´s fracture (volar angulation of the fracture)
- Does not understand written and spoken guidance in local languages
- Pathological fracture or (previous) fracture in the same wrist, antebrachium or elbow
  1. **RANDOMISATION**

All patients will be randomized before closed reduction of displaced fractures and immobilization without reduction of non-displaced fractures to either functional cast or flexion-ulnar deviation cast for 5 weeks. Patients will be randomized using a random number matrix in block allocation fashion. The blocks will be stratified by the known associations; age, centre and intra or extra-articular fracture line. The treatment allocations from the matrix will be sealed in envelopes, which are located in the ER. After the patient´s enrollment has been confirmed and informed consent is signed, a medical orderly specialized in casting will open the envelope and make the cast as allocated. The medical orderlies responsible for the casting will not participate in other ways in the study.

The research coordinator will monitor the study flow. An independent monitoring committee has been established.

- 1. **INTERVENTION**

DRFs are in everyday life treated by health care center physicians, experienced acute physicians, and trauma surgeons, thereby; we do not see any reason to limit the number of on call physicians or education or experience of on-call physician in this pragmatic trial.

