Closed reduction is done under local anaesthesia by injecting Lidocaine 1% into fracture area. The technique of closed reduction is not limited to any specific technique. Fluoroscopy can be used when performing closed reduction if it is available in the participating center. Cast reduction position examples are delivered to participating centers to assure correct position of casting. After closed reduction, additional radiographs will be taken to confirm the reduction of the fracture. After physician on-call has accepted the fracture to be treated conservatively, a dorsal splint for 5 weeks is used. Non-displaced fractures are immobilized according to randomization without reduction.

After the allocation and preparing the cast, the patient is asked to fill the PCS questionnaire.

- 1. **FOLLOW-UP**

Follow-up visits are being conducted in primary health care centers as seen necessary by the physician on-call. They are arranged by the regional guidelines, at 1 and 2 weeks with radiographs. Due to the pragmatic nature of the trial we will not set any angulation degrees or shortening limits indicating operative treatment if reduction is lost during the follow-up. Whether the achieved angulation and/or possibly restored shortening is lost during the follow-up, the decision to consult local orthopedist or hand surgeon is left to the discretion of treating physician. Moreover, if patient has been referred for operative treatment from the primary care by the physician on-call but conservative treatment is chosen in the referral center ,the patient is still eligible for the study. Follow-up of these patients is conducted in the primary care or hospital based on local protocols. Since patients will be randomized in blocks by the hospital, we will assume that randomization will take care of the possible differences between centers.

**Figure**: Flow chart of the trial.

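### The model for objective 3 adjusts the pain catastrophizing (PCS) effect for cast only, leaving it open to confounding by factors the protocol itself lists

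*Protocol*

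**What the plan says.** The Objectives section sets out, as its third aim, "to assess the effect of PCS on the functional outcome of conservatively treated DRFs", together with a possible interaction between PCS and the two cast positions. The third primary hypothesis is that "high PCS does not have an interaction with functional outcome on the patient rated wrist evaluation (PRWE) scale after adjusting for cast position used".

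The Statistical analysis section assigns the method: "Analysis of covariance will be used to assess the effect of pain catastrophizing score on the outcome of cast treatment". It then gives the terms: "PRWE will be used as a dependent variable, cast as independent and pain catastrophizing score as covariate". No other covariate and no product term is listed.

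The next paragraph describes a separate linear regression of PRWE: "Main variable of interest included is the cast and age, sex, fracture group, smoking and other diseases are used as confounding variables". PCS is not in that model. The subgroup analysis uses the same factors, again without PCS: "In subgroup analysis the effect of age, sex, fracture group, smoking, and other diseases will be evaluated against the scores".

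On how the two exposures arise, the Randomisation section states "Patients will be randomized using a random number matrix in block allocation fashion", with stratification by age, centre and intra- or extra-articular fracture line. The Intervention section states "After the allocation and preparing the cast, the patient is asked to fill the PCS questionnaire".

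**The concern.** The two exposures need different handling. Random allocation balances patient factors between casts in expectation, so a cast comparison needs no adjustment to be free of systematic confounding. Nothing balances patient factors across levels of PCS. If older, sicker or otherwise different patients score higher on PCS and also have worse PRWE, a model with cast and PCS alone will credit that difference to PCS.

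The protocol treats its five listed factors as relevant to PRWE, yet applies them only to the randomised exposure. No stated analysis gives a PCS estimate adjusted for them. At stake is the answer to objective 3 and hypothesis 3. The cast comparison is not affected.

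**Working it through.** **Comparison of the stated models**

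| Analysis | Exposure of interest | Exposure randomised? | Adjusted for |
|---|---|---|---|
| Analysis of covariance | PCS | No | Cast |
| Linear regression | Cast | Yes | Age, sex, fracture group, smoking, other diseases |

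**Inputs.** The PRWE SD is 14 and the required size is 40 per group, so 80 in all; the planned total is 104 (Power analysis). The protocol gives no correlation between the listed factors and PCS or PRWE, so joint correlations of 0 to 0.4 with each are assumed. The true PCS effect is set to zero. There is no figure in the plan to reproduce on this point.

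**Formulas**

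- Spurious correlation: r = R(factors, PCS) × R(factors, PRWE). This is a maximum. It is reached only if the same weighted combination of factors predicts both variables; otherwise r is smaller.
- Spurious slope per SD of PCS: 14 × r.
- False-positive rate, two-sided 5%, Fisher z with n = 80: put d = atanh(r) × √77; the rate is 1 − Φ(1.96 − d) + Φ(−1.96 − d).

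**Example at 0.4 and 0.4.** r = 0.4 × 0.4 = 0.16, and the slope is 14 × 0.16 = 2.24 points. d = 0.1614 × 8.775 = 1.416, so the rate is 1 − Φ(0.544) + Φ(−3.376) = 0.294.

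**Results.** The formula is set beside a simulation of the cast-plus-PCS model (3,000 runs per setting, true cast difference −11 points):

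| Assumed correlations (PCS, PRWE) | Maximum r | Points per SD of PCS | Rate by formula, n = 80 | Simulated, n = 80 | Simulated, n = 104 |
|---|---|---|---|---|---|
| 0, any | 0 | 0 | 5.0% | 5.2–5.9% | 4.5–5.3% |
| 0.2, 0.2 | 0.04 | 0.56 | 6.4% | 5.8% | 6.2% |
| 0.3, 0.3 | 0.09 | 1.26 | 12.4% | 13.2% | 13.5% |
| 0.4, 0.4 | 0.16 | 2.24 | 29.4% | 30.7% | 37.3% |

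With the confounder added to the model, the simulated PCS slope returns to about zero and the false-positive rate to 4.0–6.6% across all settings. The cast estimate stays between −10.9 and −11.1 throughout, so the primary comparison is untouched.

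**Cost in precision.** Adding the factors multiplies the variance of the PCS slope by about (1 − R²(factors, PRWE)) / (1 − R²(factors, PCS)). At 0.4 and 0.4 this is 0.84 / 0.84 = 1, so apart from degrees of freedom nothing is lost in that case.

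**The case against.** Several points can be made for the plan.

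- **No link to PCS is shown.** The Background ties catastrophizing to pain, disability, weakness and finger stiffness, not to age, sex, smoking, comorbidity or fracture type. It also says that function in elderly patients is unrelated to anatomic alignment, which weakens the route through fracture severity. A reader might infer that the PCS result *is* confounded. The documents do not support that: with no correlation there is no bias. This stands, and it limits the point to openness to confounding.
- **The model matches the hypothesis.** Hypothesis 3 names adjustment for cast only. The Background calls PCS a predictor, and Expected results and impact speaks of correlation. As a description of association, the cast-adjusted estimate is legitimate. This stands in part, but objective 3 and the analysis sentence both speak of an effect. Either the model or the wording has to change.
- **The covariates in the cast model are defensible.** A reader might conclude that they are an error there. They are not: prognostic covariates can add precision, and age and fracture line are stratification factors. Only calling them confounders of a randomised exposure is loose.
- **The size depends on the assumptions.** The upper rates are maxima under chosen correlations; at 0.2 and 0.2 the rate is near nominal. The largest slope, 2.24 points per SD of PCS, is about a fifth of the 11-point minimal important difference (2.24 / 11 = 0.20). This stands.
- **The detail may be in a statistical analysis plan.** The protocol does not exclude further covariates. However, it states the terms of both models, in adjacent paragraphs, and puts the covariates in one only. That reads as a choice rather than an omitted detail.

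**Conclusion.** The point holds as a weakness in a stated model. Objective 3 concerns a non-randomised exposure, and its only stated adjustment is for a randomised one. PCS is first completed after the cast is applied, so keeping cast in the model is sensible, but it does nothing about patient factors.

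Whether bias exists, and how large it is, cannot be determined from the protocol. Under assumed joint correlations of 0 to 0.4 with both PCS and PRWE, and no true PCS effect, the spurious slope is at most 0 to 2.2 points per SD of PCS, and the false-positive rate at 80 patients runs from about 5% to 29%. The upper figures should not be read as the expected error rate.

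Adjustment for the listed factors would not settle causation either. The Background associates acute pain and trauma-related anxiety with finger stiffness alongside catastrophic thinking, and neither is on the list. The result is best reported as an adjusted association. The matter deserves correction, but it concerns a non-primary objective.

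**What to change.** Replace the description of the PCS analysis with the following:

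1. Fit PRWE on cast, first-recorded (baseline) PCS, age, sex, fracture group, smoking and other diseases. Centre may be added as a stratification factor.
2. Report the PCS coefficient with its 95% confidence interval as an adjusted association.
3. In a second step add a cast-by-PCS term, which the interaction part of objective 3 requires and the stated model lacks.
4. State that PCS values from 3 months, 1 year and 2 years are not used as the predictor. They are recorded alongside PRWE, so the direction of influence cannot be separated.
5. Show the cast-plus-PCS model for comparison.

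The cost is a few sentences, one more model and some degrees of freedom. With one parameter per listed factor, the main model has 8 parameters (intercept, cast, PCS and five factors), leaving 80 − 8 = 72 residual degrees of freedom. Centre, with three hospitals, would take two more. Factors with more than two categories would also take more. The five factors are already planned for the other regression, so no new data are needed.

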In Finnish population aged 60 years or more the incidence of DRF can be estimated to be 126-190 per 100 000 person years [38,39]. We need to recruit more than 100 patients as suggested by the power calculation. Time for accrual in a single center is estimated to be too long; therefore to be able to enroll sufficient number of patients we are conducting a multicenter study. This study will be carried in Tampere University hospital, in Central Finland Central hospital and Satakunta Central hospital. Tampere has a catchment area with a population of 300 000 people who in case of an emergency are referred to emergency department located in the Tampere University hospital. The two latters have a catchment area with a population of 100 000 to 150 000 people who are referred to Central Finland and Satakunta Central hospitals in case of an emergency. With the incidence indicated above, we’ll identify 650-950 DRFs among elderly patients aged 60 or more within one year. Therefore we assume to finish recruiting study patients within one year.

We have homogeneity between centers with solid trial designs, data and project management including monitoring. A site personnel training has been carried out. We have been assisted by local research centers. Stability of the trial has been maintained with regular mails where researchers have shared concerns, problems and successes. Regular annual meetings (twice a year, previous on Jan 15, 2016 in Stockholm) will motivate the research team and maintain stable quality in treating. Meetings also include presentations of future studies and trials, methodology and scientific meanings will be debated. Homepage of the research team including current trial (www.nitep.eu) is under coding.

1. **Expected results and impact**
2. We expect to observe better functional outcome after functional cast treatment compared to flexion -ulnar deviation retention cast
3. We expect to observe better grip strength, quality of life, less cast changes and smaller pain in VAS with functional cast compared to flexion-ulnar deviation retention cast
4. Functional outcome is assumed to correlate with PCS regardless of treatment modality
5. After publishing these results we aim to support the creation and dissemination of trustworthy guidelines by health authorities and professional organizations.

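### Follow-up PCS is compared without its first reading and the PRWE regression on cast omits PCS, while the first PCS is taken only after casting; some precision is lost at little cost to recover

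*Protocol*

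**What the plan says.** The Study design section lists the secondary outcomes, among them "pain in visual analogue scale (VAS), PCS, quality of life (15-D), complications". The assessment table under Follow-up schedules PCS at baseline, 3 months, 1 year and 2 years. It is the only patient-reported scale with a baseline entry; PRWE is first recorded at 3 months.

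The Statistical analysis section sets out three analyses that bear on this point:

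- **Group comparisons of continuous variables.** Mann-Whitney for skewed variables, and "t-test is used when variables are unskewed". No covariate is named, and no separate method is given for PCS.
- **An ANCOVA introduced to assess the effect of PCS.** "PRWE will be used as a dependent variable, cast as independent and pain catastrophizing score as covariate". The PCS time point is not stated.
- **A linear regression for the cast effect on PRWE.** "Main variable of interest included is the cast and age, sex, fracture group, smoking and other diseases are used as confounding variables". PCS is not in the list.

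Under Expected results and impact the protocol adds: "Functional outcome is assumed to correlate with PCS regardless of treatment modality". The Intervention section has the patient complete the first PCS once allocation has happened and the cast has been made. The flow chart agrees, placing PCS in the allocation boxes.

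**The concern.** Two comparisons do not use a reading that the trial collects anyway.

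First, PCS at follow-up is the one outcome with its own early value, and the stated test ignores it. The difference between arms then has a wider interval than it needs, and it moves with any chance imbalance in the first PCS.

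Second, PRWE has no baseline measurement. PCS is the only early score the protocol expects to go with function, but the regression built around the cast effect omits it. The model that does contain PCS omits age, sex, fracture group, smoking and other diseases. No stated model uses all of them.

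Two further gaps affect any use of PCS as a covariate. The ANCOVA could be run with a follow-up PCS, which the cast may have influenced. The first PCS is itself answered in the allocated cast. At stake is precision and a clearly defined covariate, not the validity of the randomised comparison.

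**Working it through.** **Inputs.** Power analysis gives the effect to be detected: "minimal clinically important difference in PRWE was set at 11 points with SD of 14". It then gives the size before any allowance for losses: "Based on power calculations (Cl 95%, power 0.95, SD 14) required sample size per group is 40 patients". Allowing for a 30% loss, the section arrives at 52 in each arm, 104 in all. The 95% confidence level is read as a two-sided 5% test. The correlation ρ between the first PCS and PRWE, or between the first and a later PCS, is not in the protocol; it is assumed over 0.2 to 0.7.

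**Step 1, the plan's own figure.** For a difference of 11 and SD 14 with 95% power, the normal approximation gives 43 per group and the t-test gives 43.08, so 44, against the stated 40. Power at 40 per group is 93.5% (t-test). The 52 is 40 × 1.3. These are separate matters; they only set the starting point here. Taking the stated 30% loss from 52 leaves 52 × 0.7 = 36.4, so about 36 evaluable per group.

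**Step 2, PRWE adjusted for the first PCS, relative to no covariate.** Residual SD = 14 × √(1 − ρ²). Power is from the noncentral t distribution.

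| ρ (assumed) | Residual SD | Power, 36 per group | Power, 40 per group |
|---|---|---|---|
| 0 | 14.00 | 90.8% | 93.5% |
| 0.2 | 13.72 | 91.9% | 94.3% |
| 0.3 | 13.36 | 93.1% | 95.3% |
| 0.4 | 12.83 | 94.8% | 96.6% |
| 0.5 | 12.12 | 96.7% | 98.0% |

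The 95% half-width at 36 per group is 1.994 × SD × √(2/36). It is 6.6 points with no covariate, 6.3 at ρ = 0.3 and 5.7 at ρ = 0.5. The interval narrows by 1 − √(1 − ρ²): 4.6% at 0.3 and 13.4% at 0.5.

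**Step 3, follow-up PCS adjusted for the first PCS.** The protocol gives no SD or target difference for PCS, so take an effect that has 80% power unadjusted and divide the SD by the same rule. Power becomes 83.6% at ρ = 0.3, 89.9% at 0.5 and 97.5% at 0.7. The variance factor 1 − ρ² is 0.91, 0.75 and 0.51.

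**Step 4, what the figures do not show.** Step 2 compares no covariate with PCS alone. The planned ANCOVA would already deliver that gain if its cast coefficient were read off. Adding PCS to a regression that holds five other covariates gains only what PCS explains beyond them. That cannot be computed from the protocol and may be smaller.

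**Step 5, timing.** Intervention places the first PCS after allocation and casting. Background describes the flexed position as tightening the extensor tendons and raising carpal tunnel pressure. An effect of cast position on the answers is therefore conceivable, and conditioning on such a reading could remove or distort part of the cast effect.

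**The case against.** The strongest reply is that a PCS-adjusted cast effect on PRWE is already planned, whatever question the ANCOVA was written for. This stands. A reader might infer that the precision from PCS is wholly lost for PRWE; the ANCOVA paragraph rules that out. What remains is that the regression centred on cast omits PCS, the two covariate sets are never combined, and the PCS time point is open.

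A second reply is that leaving PCS out of the cast comparison is defensible because the first reading follows casting. This also stands. It means that the PCS-adjusted coefficient should not be presented as the cast effect without either a change of timing or a stated limit.

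Third, PCS as a predictor in this population is a question under test: Background says it has not been studied there, and the stated expectation gives neither strength nor time point. Hence ρ is only assumed, and at 0.3 or below the gain is small.

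Fourth, the second objective does not name PCS among the between-cast comparisons, and covariates for a secondary scale might be left to an analysis plan. The Study design section does list PCS as a secondary outcome, however, and the protocol fixes an unadjusted test for continuous variables, so the point concerns what is written.

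Finally, unadjusted tests are valid under randomisation and their intervals already allow for chance imbalance. A reader might infer bias or an invalid test; nothing in the protocol supports that.

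**Conclusion.** The point holds as a cheap improvement in efficiency and clarity. Follow-up PCS is set to be compared without its first value, and the PRWE regression on cast omits PCS. The planned ANCOVA makes the PRWE loss partial but leaves its PCS time point unstated. The first PCS, taken after casting, is not a clean pre-randomisation covariate.

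For PRWE with 36 per group, the gain relative to no covariate is 2.3 power points at ρ = 0.3 (90.8% to 93.1%) and 5.9 at ρ = 0.5 (to 96.7%); beyond the existing regression covariates it may be less. For follow-up PCS, 80% power would become 83.6% to 97.5% for ρ from 0.3 to 0.7. All of this rests on assumed correlations, a two-sided 5% test, the protocol's difference of 11 and SD of 14 for PRWE, and a first PCS that cast position has not affected.

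**What to change.** 1. Have the already scheduled first PCS completed after consent and before the allocation envelope is opened, and amend the Intervention section and flow chart to match.
2. Compare follow-up PCS between arms by ANCOVA with that first PCS as covariate.
3. Add the first PCS, never a follow-up PCS, to the covariates of the PRWE regression on cast, and state that the planned ANCOVA uses the same reading.
4. If the timing cannot be changed, state that the first PCS is a post-allocation reading and report the unadjusted estimate next to the adjusted one.

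The cost is one degree of freedom per model, a rule for patients with a missing first PCS, and a small change to the order of procedures in the emergency room. No new questionnaire or visit is needed.
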